### Sample size and power calculations

The RCT was designed to enroll an average of 6 patients for each of 56 participating clinicians. The sample size was calculated on the basis of our primary hypothesis, that the intervention group (motivation feedback) would be more effective than the control group (treatment as usual) in enhancing treatment engagement, as measured with the Service Engagement Scale (primary outcome) at 12 months after baseline assessment. The difference between the motivation feedback group and control group for the primary outcome is based on a power of 0.80 and an alpha of 0.05 (two-tailed). Earlier studies regarding differences between feedback and treatment as usual (control) conditions have shown effect sizes (standardized mean differences) ranging from 0.34 to 0.92 [16,17], but were based on treatment progress and not (solely) on treatment motivation. One RCT studying the effects of treatment adherence therapy in patients with psychotic disorders used the SES as outcome measure and found an effect size of 0.39 [80]. Therefore, we expect an effect size of approximately 0.40. Using an unpaired t-test statistic, this resulted in a minimum of 123 subjects per condition. However, as patients are clustered within clinicians, and clinicians are clustered in teams, the patient and clinician observations can not be considered as independent of each other. The sample size was therefore adjusted by the (variance inflation) factor f = 1 + (m – 1)ρ, to account for the variance that would have been achieved had there been no clustering. The cluster size (m) is 6 (patients per clinician) and the within-cluster correlation (ρ) was estimated from a previous study to be around 0.07 [21]. Thus, the computed sample size was inflated by 1.35 to be at least 166 subjects per condition (minimally 332 in total). The SES is rated by clinicians and so we expect minimal loss to follow-up on the primary outcome, but to be on the safe side we will aim for 350 patients as the total sample size.

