**Figure 3 F3:**
[figure not shown]
Flowchart of MotivaTe-IT procedures.

After having received informed consent from the clinicians, randomization will be performed at either clinician-level or team-level. Where clinicians work in FACT-teams, randomization will be performed at team-level so that a whole team (all clinicians working in this team) will be allocated to either the TAU condition or motivation feedback condition. As teams often work with a shared caseload between clinicians in the same team, this decision was made in order to prevent possible cross-over of the feedback-condition to the TAU condition within teams. Where clinicians work in an outpatient clinic on a one-to-one basis (individual case-management) then randomization will be performed at the clinician-level. The allocation ratio is 1:1 (i.e. therapist vs. therapist and team vs. team, respectively). Stratification for diagnosis in advance was considered unrealistic and impractical, as we would then have to achieve equal numbers of each patient diagnosis in each treatment condition, while our randomization is at team-level and clinician-level. Therefore, we chose to use multivariate modelling with diagnosis as a covariate (see section 2.9 ‘Statistical analyses’). Randomisation will be performed by assigning each randomization unit (e.g. a team or a clinician) a unique number, which is entered in a computerized randomization program (http://www.randomization.com) that randomizes each unit to a single treatment by using randomly permuted blocks. The randomization is single-blind, as both the principal investigator and clinicians need to know which condition the clinicians are in, in order for the clinicians to receive the necessary training for the intervention condition (or not). As a consequence, only patients will be blind to treatment allocation at baseline assessment, while clinicians are not. Due to the nature of the trial, follow-up assessment can not be blinded.

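### The base sample size of 123 per condition does not follow from the stated effect size, power and alpha, which give 100; the error is on the safe side

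*Protocol article*

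**What the plan says.** All the inputs are in the protocol article under Sample size and power calculations. The comparison of the two groups on the SES "is based on a power of 0.80 and an alpha of 0.05 (two-tailed". Two sources are offered for the effect size. Earlier feedback studies "have shown effect sizes (standardized mean differences) ranging from 0.34 to 0.92", and a trial of adherence therapy in psychotic disorders "used the SES as outcome measure and found an effect size of 0.39 [80". From these the article concludes: "Therefore, we expect an effect size of approximately 0.40". The next sentence gives the result: "Using an unpaired t-test statistic, this resulted in a minimum of 123 subjects per condition".

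The article then allows for clustering with 6 patients per clinician and a within-cluster correlation of 0.07. This gives a factor of 1.35, 166 per condition and a minimum of 332 in total. It raises the total to 350 as a margin, noting that little loss is expected because clinicians rate the SES. Allocation is 1:1 (Procedures and randomization). No other adjustment is described between the effect size and the figure of 123.

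**The concern.** The paragraph names the test, effect size, power, alpha and resulting sample size. With allocation fixed at 1:1, any four of these determine the fifth, and here they do not agree. This is not detail left to a fuller document, because the article gives both the inputs and the result.

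The point at stake is how the trial's sensitivity is read. Someone interpreting a null result on the SES would take 0.40 at 80% power as what the trial was built to detect, whereas 123 per condition before inflation implies a smaller detectable effect. Anyone reusing the calculation for a similar trial would copy a base figure that its inputs do not support.

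**Working it through.** **Inputs.** Effect size d = 0.40 (0.39 in the cited SES trial), power 0.80, two-sided alpha 0.05, unpaired t-test, cluster size m = 6, ρ = 0.07 and target 350, all from Sample size and power calculations; 1:1 allocation from Procedures and randomization.

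**Step 1: the plan's own inflation.** f = 1 + (m − 1)ρ = 1 + 5 × 0.07 = 1.35. Then 123 × 1.35 = 166.05, given as 166, and 2 × 166 = 332. This step reproduces.

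**Step 2: the base figure.** By the normal approximation, n per condition = 2(z₀.₉₇₅ + z₀.₈₀)² / d² = 2 × (1.960 + 0.842)² / 0.40² ≈ 98.1, so 99. The exact noncentral-t solution for the named test is 99.08, so 100. The stated 123 does not reproduce: 123 / 100 = 1.23, an excess of 23%.

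**Step 3: could another reading give 123?** Noncentral-t results per condition, rounded up, except where noted:

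| Variant | n per condition | Fits the text? |
|---|---|---|
| d = 0.40, 80%, two-sided 5% | 100 | as stated |
| d = 0.39 | 105 | cited SES trial |
| d = 0.36 | 123 | value not stated |
| d = 0.34 | 137 | low end of cited range |
| d = 0.40, power 85% | 114 | contradicts 0.80 |
| d = 0.40, power 90% | 133 | contradicts 0.80 |
| d = 0.40, two-sided 2.5% | 121 | contradicts 0.05 |
| d = 0.40, one-sided 5% | 78 | contradicts two-tailed |
| d = 0.40, 19% loss: 99 / 0.81 (normal approximation) or 100 / 0.81 | 123 or 124 | no such rate stated |

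The variants that reach or come close to 123 all need an input that the text contradicts or does not give.

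**Step 4: what 123 implies.** With 123 per condition, power at d = 0.40 is 0.878, and the effect detectable at 80% power is 0.359.

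**Step 5: carried forward.** From the stated inputs, 100 × 1.35 = 135 per condition and 2 × 135 = 270 in total, against the stated 166 and 332.

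**Step 6: what the target gives.** 350 / 2 = 175 per condition, and 175 / 1.35 = 129.6 effective. Power at d = 0.40 is 0.894, and the detectable effect at 80% power is 0.349. These figures assume no loss and the plan's own design effect.

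**The case against.** The strongest defence is that the effect size is only approximate, that a value of 0.36 rounds to 0.4 at one decimal, and that the error costs nothing because it makes the trial larger. The first part fails. The article writes the value to two decimals and rests it on 0.39, which needs 105. Clustering cannot already be inside 123, since the 1.35 factor is applied afterwards. Loss is dealt with only at the step from 332 to 350. Adjusting for the baseline score, as planned under Statistical analyses, does not explain it either: that would ordinarily lower the required number, not raise it.

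The second part stands and limits the point. On the plan's own assumptions power is understated, not lost.

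A reader might infer more than the article supports, in four ways:

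- **That 166, 332 and 350 are wrong in themselves.** The first two are correct arithmetic from 123, and 350 adds a separately explained margin. Only the link from 0.40 at 80% power to 123 fails.
- **That 56 clinicians with 6 patients each conflicts with 350.** The product is 336, but 6 is an average ("The RCT was designed to enroll an average of 6 patients for each of 56 participating clinicians"). It exceeds the minimum of 332, and 350 / 56 = 6.25 is consistent with it.
- **That loss to follow-up is not covered.** The article expects little loss and adds 350 − 332 = 18 patients, or 5.1% of 350. One may think this small, but it is stated.
- **That the surplus was held back for team-level clustering or drop-out.** Nothing in the article says so, and to write it in now would be an after-the-fact rationale.

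**Conclusion.** The point holds as an internal inconsistency in the primary power statement. The stated inputs require 100 per condition, not 123, and therefore 135 and 270 after inflation, not 166 and 332. The article does not show whether a different effect size, power, alpha or an unstated allowance produced 123, so the source of the discrepancy cannot be settled from the text.

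The consequence is modest and conservative: power at 0.40 is about 0.88 at the stated minimum of 332 and about 0.89 at 350, against the 0.80 claimed. It does not follow that the trial is too small or that the target should change. These powers rest on an unpaired t-test, equal groups, no loss and the article's design effect of 1.35. They describe what its own assumptions imply and do not test whether 1.35 is adequate for a trial that randomizes some whole teams, which is a separate question.

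**What to change.** Correct the sample-size paragraph in one of two ways:

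- state which effect size, power or alpha actually produced 123; or
- replace 123 by 100 and carry it through to 135 per condition and 270 in total.

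In either case keep the target of 350, and restate what it delivers under the stated design effect: about 89% power at 0.40, or a detectable effect of about 0.35 at 80% power, before any loss. The cost is one rewritten paragraph. Enrolment, randomization and the analysis are unaffected.

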### Design and setting

This study is a multicenter randomized controlled study with two treatment conditions: treatment as usual (TAU) and motivation feedback (additional to TAU). There will be two extensive measurement occasions for both groups: at baseline and follow-up at 12 months.

Twelve departments within the Mental Health Center West North Brabant (MHC WNB), and the Mental Health Center BreBurg (MHC Breburg) located in the south west of the Netherlands, were approached to participate in the study. The MHC WNB and MHC Breburg provide mental health care to varying patient populations, including patients with a primary diagnosis of psychotic and/or personality disorder who will be targeted for this study. The current study will take place at several treatment locations of the MHC WNB and MHC Breburg, and represents a partnership between these centers and the Epidemiological and Social Psychiatric Research institute (a research center within the Erasmus Medical Center in Rotterdam, the Netherlands).

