### Procedures and randomization

Figure 3 shows the study procedures. Eligible clinicians and patients will mainly be approached via specific treatment programs that provide FACT (for a description of FACT see the section on Treatment As Usual). Clinicians who are willing to cooperate in this study will be informed by the principal investigator regarding the goals and procedures of the study and receive an information brochure. Two weeks after having received the information brochure, clinicians will be contacted to ask for participation and to sign informed consent.

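### The sample size allows for clustering by clinician but not by FACT team, and its base of 123 per arm does not follow from an effect of 0.40, so the stated 80% power is unsupported

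*Protocol article*

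**What the plan says.** Under Sample size and power calculations, the difference on the Service Engagement Scale (SES) at 12 months is "based on a power of 0.80 and an alpha of 0.05 (two-tailed"). The authors write "Therefore, we expect an effect size of approximately 0.40" and then "Using an unpaired t-test statistic, this resulted in a minimum of 123 subjects per condition". They note that patients are nested in clinicians and clinicians in teams. They then apply f = 1 + (m − 1)ρ, in which "The cluster size (m) is 6 (patients per clinician") and "the within-cluster correlation (ρ) was estimated from a previous study to be around 0.07". This gives 1.35, 166 per arm and 332 in total, raised to a target of 350. The plan is for 56 clinicians with 6 patients each on average.

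Under Procedures and randomization, the recruitment route is given as "Eligible clinicians and patients will mainly be approached via specific treatment programs that provide FACT". For clinicians in such teams, "randomization will be performed at team-level so that a whole team (all clinicians working in this team) will be allocated" to one condition. Only clinicians who work one-to-one in an outpatient clinic are randomised individually.

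**The concern.** The cluster in the design effect is the clinician. On the main recruitment route the unit randomised is the team, which holds several clinicians with about 6 patients each. Any correlation between patients of different clinicians in one team adds to the variance of the treatment comparison, and the formula leaves it out. It also makes no allowance for a small number of randomised units, which reduces the degrees of freedom of the test.

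The target of 350 and the reading of the primary result both rest on this paragraph. If team-level correlation is more than slight, a null result would be taken as stronger evidence against an effect of 0.40 than it is. The Statistical analyses section only proposes to explore FACT teams as a random factor, so it does not settle the matter.

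A second error in the paragraph works in the opposite direction: the starting figure of 123 is too large for the stated inputs.

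**Working it through.** **Inputs from the article:** d = 0.40; two-sided α = 0.05; power 0.80; base 123 per arm; m = 6; ρ = 0.07; 56 clinicians; target 350 (175 per arm).

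**Assumptions, not in the article:** team ICC 0.01 to 0.05; 5 clinicians per team; 50% to 100% of patients in teams. The value of 5 comes from 56 clinicians over about 12 units (56/12 ≈ 4.7). The nearest figure in the article is "Twelve departments within the Mental Health Center West North Brabant" and its partner centre, which were approached. They are not said to be teams.

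**1. The plan's own figure.** The inflation step reproduces: 1 + 5 × 0.07 = 1.35, and 123 × 1.35 = 166. The base does not:
- n per arm = 2 × (1.960 + 0.842)² / 0.40² = 98.1, so 99; the t-test gives 100.
- Using d = 0.39, the effect cited from the earlier SES trial, gives 104.
- At d = 0.40, 123 per arm has power of about 0.88. It gives 80% power for d of about 0.36.

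**2. The hidden slack.** Power = Φ(0.40 × √(n / (2·DE)) − 1.96), where n is per arm and DE is the design effect.
- n = 166, DE = 1.35: 0.88.
- n = 175, DE = 1.35: 0.90.
- Largest DE that 175 per arm tolerates at 80% power: 175/99 = 1.77. With a t reference on 10 degrees of freedom it is about 1.45.

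**3. Adding the team level, all patients in teams.** With k clinicians per team, DE = 1 + (m − 1)ρ_clinician + m(k − 1)ρ_team = 1.35 + 24·ρ_team. At 30 patients per team, 350 patients fill about 12 teams, hence 10 degrees of freedom.

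| Team ICC | DE | Power, normal | Power, 10 df | n per arm for 80% (99 × DE) |
|---|---|---|---|---|
| 0.01 | 1.59 | 0.84 | 0.76 | 158 |
| 0.03 | 2.07 | 0.74 | 0.65 | 205 |
| 0.05 | 2.55 | 0.65 | 0.56 | 253 |

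The slack is used up at a team ICC of (1.77 − 1.35)/24 ≈ 0.018 by normal approximation, or (1.45 − 1.35)/24 ≈ 0.004 with 10 degrees of freedom.

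**4. Mixed randomisation.** With a fraction f of patients in teams and the rest clustered by clinician, effective n per arm = 175 × [f/DE + (1 − f)/1.35]. The number of units is 350f/30 + 350(1 − f)/6, which is 35 at f = 0.5 and about 26 at f = 0.7.

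| Share in teams | Team ICC 0.01 / 0.03 / 0.05, normal | Same, df = units − 2 |
|---|---|---|
| 50% | 0.87 / 0.83 / 0.80 | 0.85 / 0.81 / 0.78 |
| 70% | 0.86 / 0.80 / 0.75 | 0.83 / 0.77 / 0.72 |

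**5. Baseline covariate.** Dividing the variance by 1/(1 − r²), for an assumed baseline-to-follow-up correlation r of 0.3, 0.5 or 0.7, gives power 0.78, 0.85 or 0.95 with all patients in teams and team ICC 0.03 (0.69, 0.77 or 0.91 with 10 df).

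**The case against.** The strongest reply is that no shortfall has been shown, and this stands. A reader might infer that the trial is underpowered and that the 80% is false. The article does not support that: it fixes neither the number of teams, their size, the team-level ICC nor the share of patients in FACT teams. An article may leave the number of teams to the full protocol, so its absence is not the complaint. At team ICC 0.01 with all patients in teams, power is 0.84 by normal approximation. With half the patients in teams it stays at or above 0.80 across the whole range, although with unit-based degrees of freedom it reaches 0.78 at team ICC 0.05. The planned baseline SES covariate could recover more.

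A reader might also scale 123 by the larger design effects and conclude that 196 to 314 per arm are needed. That repeats the base error: at d = 0.40 those sizes give about 0.88 power, and the 80% figures are 158 to 253.

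It may be argued further that, because clinicians score the SES, rater leniency pushes the clinician ICC above 0.07. The direction is reasonable, and the Background does not list the SES among the outcomes of the study that supplied 0.07. The size is unknown. A clinician ICC of 0.15 would give DE 1.75, still within 1.77 and with power 0.81; 0.20 would give DE 2.00 and 0.75. Neither value has a source in the article.

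The reply does not remove the mismatch. The calculation is given in full, it names the team layer, and it omits that layer for the main recruitment route. The excess in the base is unexplained, so it cannot count as a planned allowance for teams.

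**Conclusion.** The point holds in limited form. The stated 80% power at d = 0.40 is unsupported, because the design effect uses a cluster that is not the randomised unit for FACT teams, and because 123 per arm does not follow from the stated inputs. The two errors partly offset each other. Under the assumptions above (5 clinicians per team, clinician ICC 0.07, team ICC 0.01 to 0.05, no covariate credit), power by normal approximation runs from 0.87 down to 0.75 with 50% to 70% of patients in teams, and from 0.84 down to 0.65 with all in teams. The lowest figure, 0.56, needs all patients in teams, team ICC 0.05 and 10 degrees of freedom together. A shortfall is plausible, and how large it would be depends on figures the article does not give.

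**What to change.** Do not enrol more patients on this ground. Rewrite the paragraph as follows:

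- Correct the base from 123 to about 100 per arm, or state the effect size or power that 123 was meant to serve.
- Compute the design effect with the team as cluster, with terms for both clinician and team, where teams are randomised. Keep the clinician as cluster elsewhere.
- Replace the single 0.80 by a power range over stated assumptions for the share of patients in teams, team ICC and clinician ICC. Take the degrees of freedom from the number of randomised units.
- If credit is taken for the baseline SES covariate, state the assumed correlation.

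The cost is one rewritten paragraph and a less favourable, less certain power statement.

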### Statistical analyses

The data of the RCT will be analyzed according to the intention-to-treat principle. Baseline comparability between the intervention group and control group in demographic and clinical variables will be evaluated with independent samples t-tests and chi-square tests. Furthermore, non-responders (i.e. eligible patients who chose not to participate in the study) will be compared to responders with respect to background demographic and clinical variables with independent samples t-tests and chi-square tests. Logistic regression analysis will be applied to test for differences between the motivation feedback and control group with respect to the primary and secondary outcomes that are dichotomous variables, while (multiple) linear regression analysis will be used in case of continuous outcome variables. For individual categorical outcome variables, the effectiveness will be determined by odds ratios, including p-values (two-tailed). The effectiveness of the variables combined will be determined by ROC-curves (for categorical outcomes) and the individual odds ratios, R2 and the individual regression coefficients (for continuous outcomes). The Hosmer and Lemeshow goodness-of-fit test will be used in case of logistic regression. In case of multiple regression analysis the classical regression diagnostics will be applied for normality, (non)linearity, heteroscedasticity, (influential) outliers and interaction. A subgroup analysis will be performed for patients with psychotic disorders for the effects of the intervention upon their antipsychotic medication adherence. The analyses will be performed both unadjusted and adjusted for baseline differences of the distributions between the two treatment groups. In analyzing a specific outcome variable, the baseline score of that variable will be used as covariate. The analysis will be extended using multilevel analyses that takes the nesting of measurements into account. A clustering of outcomes is likely since a single clinician may treat several patients, and clinicians are clustered into teams. Multilevel modelling will be performed to check for any clustering effects on the primary outcome. In the multilevel analyses we consider the two measurements as the first level and the patient as the second level. We will explore whether the different treatment locations (FACT teams) and institutions (MHC Breburg and MHC WNB) can be considered as random factors in the modeling. We will identify predictive factors in estimating the outcome and whether there are predictive factors dependent on the type of treatment condition (interaction between baseline variables and treatment effect). Furthermore, we will take into account to what extent patients were exposed to the intervention by analyzing the dose-effect relationship. We expect (as is the case in most empirical studies in a psychiatric setting) that missing data will occur. We expect that the data will be Missing At Random (MAR), which is allowed to be a function of the observed variables (both covariates and outcome variables). If the assumption of MAR is violated, the pattern mixture model approach will be applied. In case predictor variables are missing, the method of multiple imputations or the maximum likelihood estimation method will be applied.

For monthly measurements (i.e. the motivation feedback graph for patient and therapist, and the therapist motivation) the method of mixed modelling will be applied. This highly flexible method enables two level models: repeated measurements (level 1) and patient level (level 2).

The three motivational theories will be modelled with Structural Equation Modelling (SEM), in order to study their fit to the empirical data, their predictive power and parsimony (i.e. whether the model can be simplified without substantially reducing the model fit and predictive power). The three motivational theories will be studied exploratively to determine which theoretical constructs are most plausible (i.e. clinically relevant and statistically significant) for the prediction of the outcome variables. The difference of the two -2log-likelihood tests (including the difference of degrees of freedom) will be used for testing differences between nested models, and information criteria will be used for differences between non-nested models (i.e. Akaike Information Criterion/AIC, Bayesian Information Criterion/BIC and adapted BIC). Where relevant, the 95% confidence intervals and/or P-values (two-tailed) will be reported.

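### The named test of the primary outcome is single-level regression; the randomised unit is at best an exploratory random factor (team) and is never named as a level (clinician)

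*Protocol article*

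**What the plan says.** **Design.** Under Procedures and randomization, in FACT settings "randomization will be performed at team-level so that a whole team (all clinicians working in this team) will be allocated" to one arm. In one-to-one outpatient clinics the individual clinician is randomised.

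**Sample size.** Sample size and power calculations accepts that patients within clinicians, and clinicians within teams, are not independent. It inflates N by 1 + (m - 1)ρ with m = 6 patients per clinician and ρ = 0.07.

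**Analysis.** The Statistical analyses section states, in this order:
- For group differences, "multiple) linear regression analysis will be used in case of continuous outcome variables". The SES is such an outcome.
- A baseline rule: "In analyzing a specific outcome variable, the baseline score of that variable will be used as covariate".
- An extension to multilevel analysis, with its purpose: "Multilevel modelling will be performed to check for any clustering effects on the primary outcome".
- The levels of that extension: "In the multilevel analyses we consider the two measurements as the first level and the patient as the second level".
- An intention to explore whether FACT teams and the two institutions can serve as random factors.

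Clinicians are mentioned there as a source of clustering, but not as a level or a random factor. Nothing says whether the regression or the multilevel model gives the primary result.

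**The concern.** The analysis does not match the design. In a cluster-randomised trial the treatment effect is estimated between clusters, so its standard error must carry the between-cluster variance. Single-level regression leaves that variance out. A model with only measurements nested in patients leaves it out too, because it allows for correlation within a patient but treats two patients of the same clinician as independent.

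The clinician matters in three ways here: as the randomised unit in the outpatient clinics, as the cluster used in the sample size, and as the rater of the SES for all of his or her study patients. The team is the randomised unit elsewhere.

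If the plan is followed as worded, the standard error of the SES effect could be too small, and a nominally significant result could reflect differences between raters or teams. Making the cluster terms depend on a look at the data does not solve this, because clustering follows from the design and a check can easily miss it.

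**Working it through.** **Inputs from Sample size and power calculations.** The calculation is "based on a power of 0.80 and an alpha of 0.05 (two-tailed"), with standardised effect 0.40, 123 per condition before clustering, m = 6, ρ = 0.07, and 56 clinicians.

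**1. The plan's own clustering step.** Design effect DE = 1 + (6 - 1) × 0.07 = 1.35. Then 123 × 1.35 = 166.05, so 166 per condition and 332 in total. This reproduces. The starting value of 123 does not: effect 0.40 gives 99 per arm (normal approximation) or 100 (t-test). That is a separate matter. It errs on the large side and does not enter the error rates below.

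**2. Type I error if clinician clustering is not modelled.** The standard error is understated by √1.35 = 1.16. True two-sided error = 2 × [1 - Φ(1.96/√DE)] = 2 × [1 - Φ(1.687)] = 9.2%. Other values of ρ at m = 6:

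| ρ | DE | True error |
|---|---|---|
| 0.01 | 1.05 | 5.6% |
| 0.02 | 1.10 | 6.2% |
| 0.05 | 1.25 | 8.0% |
| **0.07 (protocol)** | **1.35** | **9.2%** |
| 0.10 | 1.50 | 11.0% |

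**3. Effect of using the baseline score.** Clinicians rate the SES at both times, so a stable rater effect partly cancels. Null simulation: 56 clinicians × 6 patients, clinicians randomised, ρ = 0.07, 8,000 runs per setting. The patient-level correlation between baseline and 12 months was assumed to be 0.5. The correlation of clinician effects over time was varied, since the documents do not give it. The change-score test is equivalent to the arm-by-time test in a model with measurements in patients only.

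| Correlation of clinician effects over time | Regression, no baseline | Regression with baseline | Change score |
|---|---|---|---|
| 0 | 9.8% | 11.7% | 12.8% |
| 0.5 | 9.6% | 9.6% | 9.1% |
| 0.9 | 9.3% | 6.6% | 6.0% |

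All values exceed 5%. The stated two-level structure does not by itself remove the excess.

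**4. Teams randomised (illustration only).** With k clinicians per team and same-team correlation ρ_T between patients of different clinicians, DE = 1 + (m - 1)ρ + m(k - 1)ρ_T. Neither k nor ρ_T is in the documents. Assuming k = 4:
- ρ_T = 0.01: DE = 1.35 + 18 × 0.01 = 1.53, error 11.3%
- ρ_T = 0.035: DE = 1.98, error 16.4%
- ρ_T = 0.07: DE = 2.61, error 22.5%

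Simulation of the last two settings gave about 16% to 17% and 22% to 23%.

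**5. Can a check be relied on?** Take a 5% F-test for clinician variance with 56 × 6 patients and ρ = 0.07. The variance ratio is 1 + 6 × 0.07/0.93 = 1.45, and with 54 and 280 degrees of freedom the power is about 57%. Real clustering of the size the protocol assumes would be missed in some 43% of trials.

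**The case against.** The strongest reply is that the plan does not ignore clustering. It says clustering is likely, and directly after the sentence on levels it proposes to explore FACT team and institution as random factors. That stands. A reader might infer that clustering is left out altogether, and the text does not support this. Team is optional; only the clinician level is truly absent.

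Three other stronger readings are tempting and also go too far:
- **That the false-positive rate is well above 5% as a matter of fact.** This holds only if an analysis without cluster terms decides the result, and the plan names no deciding analysis. Stable rater effects could also bring the rate down to about 6%. Rates of 15% or more need an assumed team size and team correlation, and not all units are teams.
- **That the multilevel model is ill-formed because baseline SES is both outcome and covariate.** The baseline-covariate rule comes before the multilevel extension and reads naturally as a rule for the regression. The text does not apply it to the two-measurement model.
- **That the monthly models repeat the fault.** They too name only measurement and patient ("This highly flexible method enables two level models: repeated measurements (level 1) and patient level (level 2"), but only the feedback arm completes monthly measures. They contain no comparison between arms.

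It may also be said that an article leaves model detail to a fuller plan. That covers silence. Here the article states the test and the levels, and these do not fit the randomisation.

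**Conclusion.** The point holds in limited form. The only between-group test named for a continuous outcome is single-level regression. The randomised unit enters at best through exploration (team) or is not named as a level (clinician), which conflicts with the protocol's own inflation of N by 1.35.

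The size is conditional. If the regression, or the two-level model without a cluster term, decides the result, the nominal 5% is about 9% at m = 6 and ρ = 0.07. With baseline used it is about 6% to 13%, under an assumed patient-level correlation of 0.5 and a clinician-effect correlation from 0.9 down to 0. Where teams are randomised it would be higher, by an amount the documents do not allow one to fix. Because this concerns the primary comparison, it should be settled before analysis.

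**What to change.** In Statistical analyses, name one primary model for the SES:
- outcome: SES at 12 months;
- fixed effects: arm and baseline SES;
- random intercepts: the randomised unit (team, or clinician where clinicians are randomised), and clinician within team;
- these random effects kept whatever their estimate or p-value;
- a small-sample degrees-of-freedom correction, such as Kenward-Roger or Satterthwaite.

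Use the same cluster terms for between-arm tests of the secondary outcomes. Keep plain regression at most as a sensitivity analysis.

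**Cost.** No new data or patients are needed. Confidence intervals become wider, and power is somewhat lower where teams are randomised, because N was inflated for clinician clustering only.
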